## Protocol

This double-center, prospective, controlled, longitudinal open clinical trial will be performed at Department of Endocrinology and Nuclear Medicine, Medical University Graz, Austria and at Interdisciplinary Obesity Center, Kantonsspital St. Gallen, Switzerland. Both centers will follow the same protocol. Both bariatric and control group will be examined at baseline before surgery. During surgical procedure samples of subcutaneous (SAT) and visceral (VAT) adipose tissue will be obtained. In bariatric patients, repeated follow-up visits will be arranged at 1-2 weeks and 12 months after the surgery and a needle biopsy of SAT will be performed at 12-months follow-up. Control group will be examined at baseline only.

At baseline visit detailed medical history and concomitant medication, particularly diabetes duration and history of diabetes therapy will be recorded. To verify the information on diabetes history the patient’s family physician will be contacted by phone calls.

At baseline and all follow-up visits, patients and controls will be studied on three occasions after an overnight fast and procedures will be grouped as follows:

1. Biochemistry, anthropometry, vital signs and oral glucose tolerance test (visits 1,4,7)
2. Isoglycaemic intravenous glucose infusion, vital signs (visits 2,5,8)
3. Botnia clamp, vital signs (visits 3, 6 and 9) and needle biopsy of SAT (visit 9)

For study visit and procedure schedule see Table 2.

| **Groups** | **Procedure** | **Baseline** | | | **1-2 weeks** | | | **12 months** | | |
| --- | --- | --- | --- | --- | --- | --- | --- | --- | --- | --- |
|  |  | **V1** | **V2** | **V3** | **V4** | **V5** | **V6** | **V7** | **V8** | **V9** |
| Bariatric group  (n=85)  55 T2DM/30 non-DM | Medical history | x |  |  | x |  |  | x |  |  |
|  | Vital signs | x | x | x | x | x | x | x | x | x |
|  | Biochemistry | x |  |  | x |  |  | x |  |  |
|  | Anthropometry | x |  |  | x |  |  | x |  |  |
|  | OGTT | x |  |  | x |  |  | x |  |  |
|  | Isoglyc. iv.infusion |  | x |  |  | x |  |  | x |  |
|  | Botnia clamp |  |  | x |  |  | x |  |  | x |
|  | SAT needle biopsy |  |  |  |  |  |  |  |  | x |
| Control group  (non-bariatric abdominal surgery)  (n=30)  15 T2DM/15 non-DM | Medical history | x |  |  |  |  |  |  |  |  |
|  | Vital signs | x | x |  |  |  |  |  |  |  |
|  | Biochemistry | x |  |  |  |  |  |  |  |  |
|  | Anthropometry | x |  |  |  |  |  |  |  |  |
|  | OGTT | x |  |  |  |  |  |  |  |  |
|  | Isoglyc. iv.infusion |  | x |  |  |  |  |  |  |  |
|  | Botnia clamp |  |  | x |  |  |  |  |  |  |

*Table 2. Study visit and procedure schedule.*

## 3. Procedures

- **Anthropometry:** weight, height, BMI, waist circumference, waist-to-hip ratio, body composition estimation (fat mass, fat-free mass) using a dual energy X-ray absorptiometry (Lunar iDXA, GE).
- **Vital signs:** blood pressure, heart rate, body temperature
- **Biochemistry:** fasting glucose, free fatty acids, lipids, electrolytes, HbA1c
- **Oral glucose tolerance test (OGTT)** with 75g of glucose (3 hours) with measurements of plasma glucose levels at 10-min intervals. Blood samples for analysis of insulin, proinsulin, C-peptide, glucagon, GLP-1 and GIP concentrations will be taken at 0,15,30,45,60,90,120,150 and 180min to assess changes in glucose tolerance, as well as to characterize responses of the enteroinsular axis to oral glucose.
- **Isoglycaemic iv. glucose infusion** (3 hours). To quantify the incretin effect, the plasma glucose profile from OGTT will be reproduced by a variable iv. glucose 20% infusion. Plasma glucose will be measured at 5-10 min intervals, blood sampling for insulin, C-peptide, glucagon, GLP-1 and GIP measurements will be performed at 0,15,30,45,60,90,120,150 and 180min.
- **Botnia clamp (combined IVGTT and hyperinsulinaemic-euglycaemic clamp)**, which is a validated design for assessment of beta cell function and insulin sensitivity [61]. After an overnight fast and after baseline samples and SAT needle biopsy (at visit 6) have been obtained, 0.3 g/kg bodyweight of 20% glucose solution will be given at time 0 min. Blood samples for the measurement of plasma glucose, insulin and C-peptide will be obtained at -10, 0, 2, 4, 6, 8, 10, 20, 30, 40, 50 and 60min. At 60 min after the glucose bolus, hyperinsulinaemic-euglycaemic clamp will be started to evaluate insulin sensitivity. A priming dose followed by an infusion (40mU/m^2^/min) of short-acting human insulin will be applied for 120 min. Blood glucose will be clamped at the concentration of 5.0 mmol/l by a variable infusion of 20% glucose. Blood samples for measurement of plasma glucose concentrations will be obtained at 5 min interval, for measurement of insulin concentrations in 30 min intervals throughout the clamp. The mean amount of glucose infused during the last 60 min of euglycaemic clamp will be used to calculate the rate of whole-body glucose uptake.

At baseline and 180 min of the Botnia clamp blood samples for determination of cytokines and adipokines (leptin, adiponectin, TNFα, hsCRP, MCP-1, IL10, IL6, IL1ra) will be collected.

- **Adipose tissue biopsies.** Two types of biopsies will be collected during the study:
  - Intraoperative during bariatric (Bariatric group) and elective surgery (Control group) – subcutaneous (SAT) and visceral (VAT) adipose tissue. Tissue samples will be acquired by surgeon at the beginning of the surgery.
  - Needle biopsy of SAT performed at 12 months of follow-up in Bariatric group. Under local anesthesia (1% trimecain in a field block pattern) an incision (3-4 mm) will be made in the skin at the lower abdomen and a subcutaneous fat specimen (300 mg) will be obtained by needle aspiration.

Based on experimental evidence of Biobank of Medical University Graz, study-specific standard operation procedures will be developed to ensure standardized and quality-assured biopsy processing, storage and shipping at both sites.

All samples will be washed with 0.9% saline solution, divided into 10 or 3 aliquot portions by intraoperative or needle biopsies, respectively and immediately frozen in liquid nitrogen. Samples will be stored at – 80°C until use for RNA extraction and gene expression analysis using real-time PCR method. Gene expression of adipokines (adiponectin and leptin), cytokines (such as TNFα, MCP-1, IL6, IL10, IL1ra), macrophage marker CD68 or genes involved in glucose and fatty acid metabolism will be analyzed (genes may be added according to actual scientific knowledge).

A subset of samples collected in Graz will be fixed with formalin and subsequently with paraffin in form of blocks. This processing enables further histological analysis of adipocyte size or macrophage infiltration in adipose tissue.

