# Novelty and importance of the proposed work

For the first time, our study will systematically evaluate beta cell function, by using three different glucose stimulation tests, in relation to adipoinsular and enteroinsular axes early and long-term after gastric bypass. Moreover, our study will also address the important question, if surgery induced beta cell function improvement also occurs after longer duration of T2DM when reduction of beta cell mass is expected. The parallel performance of an OGTT and an isoglycemic iv. glucose infusion will allow to quantify the incretin effects and thus, to precisely define the role of incretin hormones in the improvement of beta cell function after bariatric surgery. Our findings are therefore expected to bring new knowledge on possible reversibility of beta cell damage in long-standing T2DM.

Our approach of repeated biopsy at 1 year follow-up and comparison with control group matched for expected one-year postoperative BMI shall enable to identify surgery-specific changes in gene expression in adipose tissue independent on weight loss.

The sample size of this double-centre study which also includes controls will enable to achieve sufficient power of the study to reliably detect significant differences between groups as well as to perform valid multivariate regression analysis.

It is worth to point out that only the combined effort of our two study centres will let us achieve such a large sample size recruited in an acceptable period of time.

The results are expected to provide important new insight into the pathophysiology of disturbed beta cell function and its possible restoration in T2DM. Bariatric operations such as the gastric bypass procedure provide a unique model of rapid changes in pathological beta cell function and the results of this study on the long run may help to develop rational approaches to overcome beta cell failure in T2DM also with conservative means, e.g. by pharmacotherapy.

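### In subcutaneous fat, sampling technique is aliased with the 12-month time point, so the claim to identify surgery-specific gene-expression changes independent of weight loss is not supported

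*Protocol*

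**What the plan says.** The Protocol, Methodology, 3. Procedures, defines two kinds of adipose tissue biopsy.

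- At operation, in both groups: "Intraoperative during bariatric (Bariatric group) and elective surgery (Control group) – subcutaneous (SAT) and visceral (VAT) adipose tissue". It adds: "Tissue samples will be acquired by surgeon at the beginning of the surgery".
- At follow-up, in one group: "Needle biopsy of SAT performed at 12 months of follow-up in Bariatric group". Under local anaesthetic, through a small incision in the lower abdomen, "a subcutaneous fat specimen (300 mg) will be obtained by needle aspiration".

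Samples are then "divided into 10 or 3 aliquot portions by intraoperative or needle biopsies, respectively and immediately frozen in liquid nitrogen". Standard operating procedures are promised "to ensure standardized and quality-assured biopsy processing, storage and shipping at both sites"; how the tissue is acquired is not among the items named. The section headed Protocol says: "Control group will be examined at baseline only". Table 2 accordingly gives controls no needle biopsy, and it shows no needle sample in bariatric patients before surgery.

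The section Novelty and importance of the proposed work says that the repeat biopsy at one year, together with the BMI-matched controls, "shall enable to identify surgery-specific changes in gene expression in adipose tissue independent on weight loss". Adipose tissue expression is listed among the secondary outcome variables. Section 6, Statistical analysis, assigns a Mann-Whitney U test to the comparison with controls after weight loss, and a repeated-measures ANOVA with group and time factors to changes within the bariatric groups.

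**The concern.** The claim in the Novelty section rests on two SAT contrasts: 12 months against baseline in the same patients, and 12-month bariatric patients against controls. Each sets tissue that is entirely needle-aspirated against tissue that is entirely surgical. If technique influences measured expression, that influence enters both contrasts in full and reads as an effect of gastric bypass. The gene list includes a macrophage marker and several cytokines, for which the mix of cells in the specimen could matter.

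This is not a detail that a statistical analysis plan could settle. The protocol fixes which specimens will exist, and once collection is over no model can recover a technique effect that was never observed separately from time.

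**Working it through.** **Inputs.** Three SAT conditions are sampled (Protocol, section Protocol, Table 2, and 3. Procedures). Code each by group, time and technique:

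| Condition | Bariatric | 12 months | Needle |
|---|---|---|---|
| Bariatric, at surgery | 1 | 0 | 0 |
| Bariatric, 12 months | 1 | 1 | 1 |
| Control, at surgery | 0 | 0 | 0 |

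The needle column equals the 12-month column.

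**Estimability.** Write mean log expression as a + b·Bariatric + p·(12 months) + t·Needle, where t is the technique effect.

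- 12 months minus baseline, bariatric: (a + b + p + t) − (a + b) = p + t.
- 12-month bariatric minus control: (a + b + p + t) − a = b + p + t.
- Baseline bariatric minus control: (a + b) − a = b, free of technique.

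The design matrix has rank 3 for 4 parameters. Neither p nor b + p can be estimated apart from t.

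**What remains between bariatric groups.** For two groups with changes p1 + t1 and p0 + t0, the difference in change is (p1 − p0) + (t1 − t0). This equals p1 − p0 only if t1 = t0, that is, if the technique effect is additive on the log scale and the same in both groups.

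**The other reading of the schedule.** The Botnia clamp paragraph in 3. Procedures places a needle biopsy at visit 6 (1-2 weeks). The visit list in the section Protocol and Table 2 place it at visit 9, and the biopsy paragraph in 3. Procedures places it at 12 months. A visit 6 sample would also be postoperative. It adds one condition and one parameter (four conditions, five parameters), so p and b + p stay non-estimable. Only 12 months against 1-2 weeks would be free of technique.

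**Effect of a bridging sample.** A needle sample at surgery in bariatric patients has mean a + b + t. Subtracting the surgical specimen, a + b, leaves t. The rank becomes 4 of 4 and both 12-month contrasts become estimable, under the same common additive assumption. Bridging in controls instead gives the same rank.

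**Illustration only.** The protocol states no figure for this contrast, so there is none to reproduce. Assume no true difference, a technique shift of d standard deviations, two-sided 5% testing, and 75 bariatric completers (85 × 0.88 = 74.8) against 30 controls. The standard error is √(1/75 + 1/30) = 0.216 SD, and the chance of a significant result is about Φ(d/0.216 − 1.96). The simulated column is the planned Mann-Whitney test, with 4,000 runs and normal data.

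| Assumed d | Normal approximation | Simulated |
|---|---|---|
| 0 | 5% (nominal) | 4.7% |
| 0.2 | 15.1% | 14.8% |
| 0.5 | 63.9% | 60.8% |
| 0.8 | 95.9% | 94.4% |

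The d values are assumptions; the documents support no particular one. Comparing within diabetes status would use smaller groups and give lower rates. At d = 0.5 with 50 against 15 patients, the standard error is √(1/50 + 1/15) = 0.294 SD, and Φ(0.5/0.294 − 1.96) is about 40%.

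**The case against.** The strongest reply is that nothing in the documents shows that technique changes expression. No size, direction or evidence of such an effect is given, and every false-positive percentage depends on a shift chosen by the reader. This stands: at a shift of zero the planned test behaves as it should.

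Second, handling is largely common. All samples are washed in saline, frozen at once in liquid nitrogen and stored at the same temperature, under study-specific procedures. The only stated difference is the number of aliquots. A reader might infer that processing differs between techniques, but the text does not support that. A reader might also infer that the sampling site differs. The needle site is the lower abdomen, but the intraoperative SAT site is not stated, so a difference is possible rather than shown.

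Third, the group-by-time analysis among the bariatric groups is already in Section 6. This also stands: that part of the remedy adds a stated assumption and an emphasis, not a new analysis.

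Fourth, the scope is narrow: SAT expression is one part of one secondary outcome.

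None of this answers the structural point. Common processing does not make acquisition common, and the procedures named do not cover acquisition. The group-by-time analysis answers a different question from the one the Novelty section claims to answer.

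**Conclusion.** The point holds as one of identifiability. For SAT gene expression, both 12-month contrasts are completely aliased with sampling technique (rank 3 of 4), and the statement that the design isolates surgery-specific changes independent of weight loss claims a property the design does not have. This follows from the sampling plan alone and needs no assumption about effect size.

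A reader might go further and conclude that the SAT results will be biased, or that the gene-expression work as a whole is invalid. The documents support neither. The size of any bias is unknown and could be nil. The acute insulin response, plasma adipokines and cytokines, incretins, visceral tissue, and the baseline SAT comparison of bariatric patients with controls are untouched. Differences in change between the bariatric groups remain interpretable if the technique effect is additive on the log scale and common to the groups.

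**What to change.** 1. **Wording, at no cost.** Withdraw the claim in the Novelty section, or qualify it by stating that the 12-month SAT contrasts are confounded with sampling technique.
2. **Basis for conclusions, at no cost.** Rest SAT expression conclusions on (a) baseline bariatric against control and (b) group-by-time differences among the bariatric groups in the ANOVA of Section 6. State the assumption that the technique effect is additive on the log scale and common to the groups.
3. **Optional, at a small cost in tissue.** At least in a subset, take part of the already planned intraoperative SAT specimen by the same needle technique and at the same lower-abdominal site as at 12 months, and keep the rest as surgical tissue. Technique can then be estimated within patients. The anaesthetic setting would still differ from the 12-month visit, so the correction would not be complete. Switching all intraoperative SAT to needle sampling is a poorer trade: it would cut each specimen from 10 aliquots to 3 and leave the same difference in setting.
4. **Reconcile the schedule.** The needle biopsy is placed at visit 6 in the Botnia clamp paragraph, but at visit 9 or 12 months in the section Protocol, Table 2 and the biopsy paragraph. These passages must be made to agree.

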## 4. Analytical procedures

- **Glucose concentration** in arterialized blood samples will be measured in duplicate, using two Beckman Glucose Analyzers 2 (Beckman Instruments Inc., Fullerton, CA).
- Lipids, electrolytes, HbA1c, hs-CRP and free fatty acids will be analyzed using established laboratory techniques routinely available at both sites
- **Insulin and C-peptide** will be analyzed using routinely available partly automated ELISA methods in the Laboratory for Endocrinology and Metabolism and the EndoGenLab at Medical University Graz, Austria
- **GLP-1 and GIP analysis.** Blood samples will be collected into pre-chilled tubes containing EDTA plus aprotinin. After centrifugation plasma samples will be frozen at -80 °C until analysis. Total GLP-1 and GIP levels will be determined by RIA and ELISA methods, respectively.
- **Adipokines and cytokines**: Plasma and serum samples will be frozen for the prospective analysis of cytokines as follows:
  - Adiponectin, leptin will be measured using commercially available enzymatic immunoassays (ELISA; Biovendor Research Products, Heidelberg, Germany)
  - TNF-alpha, IL6, IL10, MCP-1, IL1ra will be analyzed using commercially available multiplexed ELISA assays (R&D Systems - Minneapolis, USA) and a multiplex ELISA system (BioPlex®200, Bio-Rad Laboratories, California, USA).
- **Gene expression analysis.** Frozen tissue samples will be homogenized with Trizol in RNA-free glass tubes and centrifuged at 500g for 5 minutes. Subsequently, RNA will be extracted according to the manufacturer specifications. RNA quality control will be checked by RNA electrophoreses. Finally, RNA isolation will be performed using the RNeasy MinElute Cleanup Kit (Qiagen, Germany) and DNA will be obtained by using iScript cDNA synthesis kit (Bio-Rad, USA). Target DNA will be quantified by real-time PCR using TaqMan assay according to the specifications provided by the manufacturer (Applied Biosystems, Foster City, CA, USA).

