Besides above discussed mechanisms, changes of adipokines and inflammatory mediators from adipose tissue have been postulated to be responsible for long-term improvement in glucose metabolism after gastric bypass in relation to reduced fat mass [25]. The role of adipose-tissue derived factors in insulin resistance is widely acknowledged [26], however their relation to beta cell function is not clarified yet. Based on cell culture experiments and rodent models, experimental evidence exists that adipokines and inflammatory mediators directly interact with beta cell function through regulation of lipid and glucose metabolism in the beta cell (leptin, free fatty acids), through changes in insulin secretion (leptin, TNFα, adiponectin, free fatty acids, IL6), changes in insulin gene expression (leptin), or through modification of beta cell glucose and insulin sensitivity or beta cell apoptosis (leptin, adiponectin, IL6, TNFα) [27, 28]. An inflammatory process in islets from patients with T2DM as a response to metabolic stress with activation of the IL-1β pathway has been recently postulated to contribute to beta cell failure and enhanced apoptosis [29].

Clinical data supporting causal relationships within the adipoinsular axis are still lacking. Changes in beta cell function after bariatric surgery therefore represent a useful clinical model for investigation of adipoinsular axis. However, clinical studies dealing with changes of adipokines after bariatric surgery did not address beta cell function in parallel, and vice versa.

Plasma concentrations of leptin are consistently reported to decrease after bariatric surgery, already within 4 weeks [10, 30-32], its decline reflects long-term BMI reduction [31], but the correlation of leptin with beta cell function improvement was rarely investigated and the results are conflicting – there are both pros [10, 33] and contras [20]. An increase in plasma adiponectin after bariatric surgery is consistently found in the literature [32, 34-36], but again the relation to beta cell function has been rarely investigated with contradictory results [20, 33]. Similarly, other adipose-tissue derived cytokines and inflammatory factors (TNFα, IL6, MCP-1, hs-CRP, IL-1ra [receptor antagonist for IL1β], IL10) implicated in chronic low-grade inflammation associated with obesity, have been previously assessed after bariatric surgery [30, 37-39], but were never related to beta cell function.

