# Methodology

## Population

Bariatric group: 85 severely obese patients (55 T2DM patients and 30 non-diabetic [non-DM] patients) fulfilling the indication criteria for laparoscopic gastric bypass surgery including the personal wish to undergo gastric bypass will be consecutively recruited at the Obesity Outpatient Clinic, Medical University Graz, Austria and at Interdisciplinary Obesity Center in St. Gallen, Switzerland. In the subgroup of T2DM surgery patients, patients with wide range of disease duration will be included. Long-standing T2DM will be classified as the disease duration longer than 10 years at the time of surgery. Within the T2DM subgroup, the expected proportion of long-standing T2DM will be 40-50%. For the detailed recruitment proportions at both sites see Table 1.

Control group: 30 patients (15 T2DM patients and 15 non-DM patients) undergoing elective laparoscopic abdominal surgery in the absence of neoplastic disease, acute or chronic inflammatory disease will be consecutively recruited at both sites. The control group will be matched with bariatric group for age, sex and expected one-year postoperative BMI (BMI 27-35 kg/m^2^).

| Site | **Bariatric group (n=85)** | | **Control group (n=30)**  **(15 T2DM / 15 non-DM)** |
| --- | --- | --- | --- |
|  | **T2DM** | **non-DM** |  |
| Graz, Austria | 15 | 15 | 15 |
| St. Gallen, Switzerland | 40 | 15 | 15 |
| Total | 55 | 30 | 30 |

*Table 1. Recruitment proportions at both sites.*

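### hs-CRP and free fatty acids are left to routine methods at two centres, so a laboratory difference would partly enter comparisons of levels between groups with unequal centre mix

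*Protocol*

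**What the plan says.** Section 4 (Analytical procedures) sets the assay arrangements marker by marker:

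- Routine clinical chemistry, hs-CRP and free fatty acids: "Lipids, electrolytes, HbA1c, hs-CRP and free fatty acids will be analyzed using established laboratory techniques routinely available at both sites".
- Insulin and C-peptide are analysed "in the Laboratory for Endocrinology and Metabolism and the EndoGenLab at Medical University Graz, Austria".
- Adiponectin and leptin have a named kit: "Adiponectin, leptin will be measured using commercially available enzymatic immunoassays (ELISA; Biovendor Research Products, Heidelberg, Germany".
- The remaining cytokines also have named assays: "TNF-alpha, IL6, IL10, MCP-1, IL1ra will be analyzed using commercially available multiplexed ELISA assays". For these and for adiponectin and leptin, no laboratory is stated.

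Two of the locally handled analytes are more than clinical chemistry. Section 3 (Procedures) includes hs-CRP in the Botnia clamp set: "blood samples for determination of cytokines and adipokines (leptin, adiponectin, TNFα, hsCRP, MCP-1, IL10, IL6, IL1ra) will be collected". The Background lists free fatty acids among the adipose factors that act through "regulation of lipid and glucose metabolism in the beta cell (leptin, free fatty acids".

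The Population section refers the reader to Table 1 for the centre split ("For the detailed recruitment proportions at both sites see Table 1"). Its columns are bariatric T2DM, bariatric non-DM and control. The Graz row reads "Graz, Austria | 15 | 15 | 15", and the St. Gallen row gives 40, 15 and 15.

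Section 6 (Statistical analysis) lists group, time and, where needed, treatment as ANOVA factors. It uses a Mann-Whitney U test to compare bariatric patients after weight loss with the controls, who are examined at baseline only.

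**The concern.** Two routine laboratories can differ systematically in calibration. If each centre measures its own patients, such a difference is tied to centre. If the groups draw on the centres in different proportions, part of it appears as a group difference.

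The exposed analyses compare levels between different people: T2DM versus non-diabetic bariatric patients at a given visit, and bariatric patients at 12 months versus the controls. In these nothing cancels the offset. The Mann-Whitney test in its standard form takes no covariate, and the ANOVA factors listed do not include centre. A statistical analysis plan might add centre, so its absence here is not a fault in itself. It does mean that nothing in the protocol offsets the assay arrangement.

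At stake is the reading of hs-CRP and free fatty acids within the secondary objectives on the adipoinsular axis.

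**Working it through.** **Inputs.** Table 1 (Population section), Graz / St. Gallen: bariatric T2DM 15 / 40, bariatric non-DM 15 / 15, controls 15 / 15. The laboratory difference d is not in the documents, so it is assumed and shown as a range.

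**Table 1 reproduces.** 15 + 40 = 55; 15 + 15 = 30; 15 + 15 = 30; 55 + 30 = 85.

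**St. Gallen shares.**

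- Bariatric T2DM: 40/55 = 72.7%
- Bariatric non-DM: 15/30 = 50.0%
- All bariatric: (40 + 15)/85 = 55/85 = 64.7%
- Pooled controls: 15/30 = 50.0%

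**Formula.** Spurious difference in group means = (difference in St. Gallen share) × d.

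| Comparison of levels | Share difference | d = 5% | d = 20% | d = 30% |
|---|---|---|---|---|
| Bariatric T2DM vs bariatric non-DM | 0.727 − 0.500 = 0.227 | 1.1% | 4.5% | 6.8% |
| Bariatric T2DM vs pooled controls | 0.227 | 1.1% | 4.5% | 6.8% |
| All bariatric vs pooled controls | 0.647 − 0.500 = 0.147 | 0.7% | 2.9% | 4.4% |
| Bariatric non-DM vs pooled controls | 0.500 − 0.500 = 0 | 0 | 0 | 0 |

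On the log scale, a laboratory ratio r gives a spurious ratio of r^0.227. For r from 1.05 to 1.30 this is 1.01 to 1.06, in line with the table.

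**Controls with T2DM only.** Their centre split is not given. With k of the 15 from St. Gallen, the share difference is 40/55 − k/15. A near-even split gives 0.727 − 0.467 = 0.26 (k = 7) or 0.727 − 0.533 = 0.19 (k = 8).

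**Effect on false positives.** Let d be in units of the within-centre SD, and let a group with St. Gallen share p have variance 1 + p(1 − p)d². For T2DM versus non-DM at baseline (55 vs 30), a two-sided 5% normal test of means gives:

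- d = 0.25 SD: bias 0.06 SD, type I error 5.7%
- d = 0.5 SD: bias 0.11 SD, type I error 7.8%
- d = 1 SD: bias 0.23 SD, type I error 14.7%

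For all bariatric completers versus controls (75 vs 30), the type I errors are 5.3%, 6.3% and 9.4%. These are approximations for a comparison of means, not exact figures for a rank test.

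**Changes within a patient.** If a patient's values at baseline and follow-up both carry the same additive offset, the follow-up-minus-baseline difference does not contain it. The same holds for a constant ratio after log transformation.

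**The case against.** The strongest reply is that the protocol contains no error here. It does not say outright that each centre measures its own samples, nor that the two methods differ, and cross-calibration is often kept in a laboratory manual. That stands: local measurement is the natural reading but an inference, and the bias exists only if the laboratories differ systematically.

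The contrast with the other markers should not be overdrawn either. A laboratory is named only for insulin and C-peptide, while adiponectin, leptin and the cytokines have common kits. Free fatty acids sit under Biochemistry in section 3 and are not named as an outcome variable, so the case for them is weaker than for hs-CRP.

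A reader might also infer more than the documents support:

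- *That every group comparison is affected.* Bariatric non-diabetic patients and pooled controls have the same centre mix, so their comparison has no shift.
- *That the shift could reach 0.73 d.* That value (0.727 − 0) requires all 15 T2DM controls to come from Graz. The Population section plans consecutive recruitment of controls at both sites and nothing suggests such a split. Nor does section 6 say that the control comparison is divided by diabetes status.
- *That the planned regressions are degraded.* For the adipoinsular markers they relate changes to changes. A constant additive offset drops out, as does a constant ratio on the log scale, provided each patient stays at one centre and the method is stable. A ratio offset on untransformed data would not fully cancel, so the protection is large but not complete.
- *That the primary result is at risk.* AIR rests on insulin and C-peptide, which this sentence does not cover. The centre split of short- versus long-standing T2DM is not stated, so no imbalance can be claimed there.

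**Conclusion.** The point holds as a minor improvement to secondary markers. If hs-CRP and free fatty acids are measured locally and the laboratories differ by d, comparisons of levels shift by about 0.23 d for bariatric T2DM versus bariatric non-diabetic patients or pooled controls, and by about 0.15 d for all bariatric patients versus controls. With d assumed between 5% and 30%, the larger shift is about 1% to 7%. Against T2DM-only controls the size depends on a split that the protocol does not give.

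This rests on three assumptions: that measurement is local, that a systematic difference exists, and that recruitment follows Table 1.

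**What to change.** Amend the sentence in section 4 so that hs-CRP for both centres is measured in one laboratory, on the frozen samples already drawn with the cytokine set. Insulin and C-peptide are already assigned to Graz, so a route for central analysis exists.

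Free fatty acids need a separate provision. They belong to the biochemistry visits (V1, V4, V7), whereas the cytokine samples are taken at the clamp visits (V3, V6, V9). Either freeze a fasting aliquot at the biochemistry visit, or use the clamp baseline sample, and do the same throughout. For both markers, analyse all visits of a patient in one run. A single laboratory sets the shift to zero.

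If local assays are kept, document a cross-calibration between the two laboratories, or stratify or adjust the comparisons of levels by centre.

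The cost is small: two inexpensive assays and one aliquot per visit. The protocol does not state whether spare sample volume is available, so that should be checked.
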